## Abstract

**Background:**

Gambling disorder (GD) has become a wide concern in Indonesia, as many negative consequences arise from this psychiatric condition. Prompt treatment with an appropriate method of delivery is required to achieve optimal outcomes in GD patients. This protocol paper outlines a study to determine the effectiveness, acceptability, and feasibility of internet-based cognitive behavioral therapy (iCBT) in treating GD in Indonesia.

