**Methods:**

This non-randomized pilot and feasibility study will recruit 20 people with GD. All participants will receive the iCBT intervention through self-learning videos and guided weekly group sessions. The effectiveness of the intervention will be assessed at baseline (week 0), post- treatment completion (week 10), and 6 weeks post-treatment (week 16). The outcomes measured will be the change in gambling symptoms, gambling urges, cognitive distortions, readiness to change, emotional problems, and quality of life of the participants.

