^ Similar findings also come from an Indonesian study that indicated only 15.5% of people seek treatment for GD.
^
2
^ Problem gambling and its consequences can remain hidden within families, usually over extended periods, and help-seeking is often the last resort after significant adverse events or crises such as family breakdown, loss of employment, legal issues, or deterioration of mental health.
^
13
^
^,^
^
14
^ Since delivering treatment for gambling disorders is challenging in Indonesia due to its vast and varied territory, iCBT appears to be a promising treatment option. However, research regarding the effectiveness of iCBT is still very scarce in Indonesia. This pilot study aims to examine the effectiveness, acceptability and feasibility of iCBT for GD in Indonesia.

PROTOCOL

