### Participants and settings

A total of 20 participants screened as probable pathological gambler (indicating severe and pervasive problem gambling) based on South Oaks Gambling Screen (SOGS) will be recruited using online advertisements via social media and through consecutive sampling by directly approaching current and former patients in inpatient and outpatient services in Cipto Mangunkusumo Hospital, Indonesia. All participants will be allowed to continue their prior treatment as indicated.

The inclusion criteria include age between 18-59 years old, fluent in Bahasa Indonesia, be diagnosed as person with GD using ICD-11 by medical doctors at [name] General Hospital, Jakarta, Indonesia. Exclusion criteria are no history of gambling in the past six months, history of severe psychiatric disorder (i.e., psychotic disorders, severe mood disorders, and intellectual disability), history of neuropsychiatric disorders (e.g., seizures), and inability to access web browsers and online conferencing platforms. There will be no drop out criteria in this study. Adherence to the treatment will be evaluated to optimize the configuration of the iCBT for future studies.

The South Oaks Gambling Screen is chosen as a screening tool because of its widespread use internationally.
^
16
^ The adaptation to Indonesian version in community setting yielded a good validity and reliability testing, indicating SOGS as a good instrument to screen for GD in Indonesia.
^
2
^

Following the determination of a participant’s eligibility, several instruments will be employed to assess the effectiveness of the study. The primary outcomes will be evaluated using the Indonesian version of the Gambling Symptom Assessment Scale (G-SAS) to measure gambling symptoms, the Gambling Urge Scale (GUS) to assess gambling urges, and the Gambling Related Cognitions Scale (GRCS) to evaluate cognitive distortions. Secondary outcomes will be measured using the Barratt Impulsiveness Scale-11 (BIS-11) to assess impulsivity, the University of Rhode Island Change Assessment Scale (URICA) to gauge readiness to change, the World Health Organization Quality-of-Life Scale (WHOQOL-BREF) to evaluate quality of life, and the Self Rating Questionnaire-20 (SRQ-20) to assess emotional problems.
^
17
^
^–^
^
27
^ The assessment schedule is presented in
Table 1 and
Figure 2.

**Table 1. T1:** Outcome and measurement.

Outcome	Measurement	Data for analysis	Type and score range	Hypothesis	Assessment time point		

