To our knowledge, our study will be the first to examine the effectiveness, acceptability and feasibility of a CBT program which will be delivered online for patients with GD in Indonesia. The outcome of this study will provide valuable data for the development of iCBT for individuals with addiction, particularly GD in LMIC. This established module may be a beneficial addition to the resources of treatment for GD in practice.

Evidence-based treatments for GD in Indonesia and LMICs in general remain sparse. The proposed study may provide an alternative to conventional CBT when physical accessibility is an issue (as many experienced during the COVID-19 pandemic), or when the patients have limited access to professional help locally. As a result of this study’s findings, iCBT might be applied in a more widespread context and utilized as a module to assist psychiatrists in engaging and treating more GD patients throughout Indonesia.

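### The protocol sets out to determine the effectiveness of iCBT, but a single-arm before-after study of 20 people cannot attribute a fall in gambling scores to iCBT

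*Protocol article*

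**What the plan says.** The aim is stated causally in several places. The Abstract (Background) "outlines a study to determine the effectiveness, acceptability, and feasibility of internet-based cognitive behavioral therapy". The Introduction ends: "This pilot study aims to examine the effectiveness, acceptability and feasibility of iCBT for GD in Indonesia". The Discussion repeats the aim in its opening sentence and again where it describes the study as the first of its kind.

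The design is given in the Abstract (Methods): "This non-randomized pilot and feasibility study will recruit 20 people with GD", and "All participants will receive the iCBT intervention through self-learning videos and guided weekly group sessions". The basis for the effectiveness claim follows: "The effectiveness of the intervention will be assessed at baseline (week 0), post- treatment completion (week 10), and 6 weeks post-treatment (week 16"). Study design calls this quasi-experimental, but describes no comparison group, waiting period or repeated baseline.

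Participants and settings requires a SOGS result in the most severe category. Recruitment is by social media advertisement and by approaching current and former patients of one hospital. On other care it says: "All participants will be allowed to continue their prior treatment as indicated". The same section makes G-SAS, GUS and GRCS the primary outcomes, and Table 1 gives each a directional hypothesis. Sample size uses a matched-samples formula on GUS, with SD 11 and 5 units.

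On use of the results, the Abstract (Discussion) foresees a later conclusive trial, but in the same paragraph expects direct relevance to practice. The main Discussion says that "iCBT might be applied in a more widespread context and utilized as a module".

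**The concern.** With no control, the mean change from T1 is the sum of any iCBT effect and everything else that moves scores over 10 or 16 weeks. Three such sources are plausible here.

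- **Regression to the mean.** People entered on a severe screen may, on average, score lower later without treatment.
- **Natural recovery.** Gambling problems may ease over four months without iCBT.
- **Co-treatment.** Other care is permitted. If it starts, stops, changes or is still taking effect during the study, its effect is mixed with that of iCBT.

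The document names none of these as a limit on attribution. The primary outcomes, directional hypotheses and sample size are all built around a before-after fall, so a significant fall would naturally be read as the effectiveness result that the aim promises. Readers and funders could then credit iCBT with change that the study cannot assign to it, and the later controlled trial could be planned on an inflated effect.

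**Working it through.** **1. What the design can identify.** One group, all treated, measured at T1, T2 and T3. The estimable quantity is mean(T2 or T3) minus mean(T1). The aim requires the difference between that change and the change the same people would have had without iCBT. Nothing in the design supplies the second term, and no sample size or mixed model can recover it.

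**2. The plan's own figures.** Sample size gives Z values 1.96 and 0.84, S = 11, E = 5, and n = 19.36. Its formula gives ((1.96 + 0.84) × 11/5)² = 6.16² = 37.95. The printed 19.36 equals (2.0 × 11/5)². That discrepancy is a separate matter and this point does not depend on it; only the SD of 11 and the 5 units are used below.

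**3. Illustrative regression to the mean (assumed inputs).** Let r be the test-retest correlation of GUS, and k the number of SDs by which the group's mean at T1 lies above the usual level of the population it comes from. Neither is in the document. Expected fall with no iCBT effect = (1 − r) × k × SD, with SD = 11.

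| r | k = 0.5 | k = 1.0 |
|---|---|---|
| 0.5 | 2.75 | 5.5 |
| 0.6 | 2.2 | 4.4 |
| 0.7 | 1.65 | 3.3 |
| 0.8 | 1.1 | 2.2 |

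The range is 1.1 to 5.5 units, or 22% to 110% of the 5 units. The formula describes selection on the outcome itself. Here selection is on SOGS, and GUS is taken afterwards at T1. Regression carries over only as far as the two scales share temporary variation, so for given r and k these are upper bounds, provided that SOGS does not track the temporary part of GUS more closely than GUS itself does.

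**4. What a non-specific fall does to a significance test.** Assume no iCBT effect, n = 20, SD of change 11, and a two-sided 5% paired t test standing in for the T2-against-T1 contrast of the mixed model (noncentral t).

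| Non-specific fall (GUS units) | Probability of p < 0.05 |
|---|---|
| 0 | 5% |
| 1.1 | 7% |
| 3 | 21% |
| 5 | 49% |
| 5.5 | 57% |

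**5. Could 20 people support a controlled claim?** Taking 11 as the SD of change, n per arm = 2 × (2.80 × 11/5)² = 75.9, so 76 per arm and 152 in total. Splitting the planned 20 as 10 + 10 gives about 17% power for 5 units. Adding a control arm at this size is therefore not the remedy.

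**6. What 20 people can give.** On the same assumption, the 95% CI for mean change has half-width 2.093 × 11/√20 = 5.1 units. In a subgroup of 10, for example those with no other treatment, it is 2.262 × 11/√10 = 7.9 units, wider than the 5-unit target.

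**The case against.** The strongest reply is that this is labelled a pilot and feasibility study, that a single arm is legitimate for that purpose, and that the Abstract already points to a later conclusive trial. The first two parts stand: the design itself is not at fault. The third shows the inconsistency rather than curing it. A study that leaves the conclusion to a later trial cannot also determine effectiveness, and the same paragraph goes on to expect direct relevance to practice.

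Several stronger readings are tempting, and the document does not support them.

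- **That participants are help-seekers in crisis.** A reader might infer this from the Introduction, where "help-seeking is often the last resort after significant adverse events or crises". That sentence is general background. This sample comes from advertisements and direct approaches, and no crisis is required for entry.
- **That regression to the mean alone would produce the whole 5 units.** This needs r = 0.5 with k near 1.0, both unsourced, and a formula that overstates the effect when selection is on another scale.
- **That co-treatment necessarily biases the change.** Treatment that is stable and has reached its full effect is already present at T1. Only treatment that changes or is still taking effect matters.
- **That co-treatment goes unrecorded.** Participant characteristics does not list concurrent treatment, but it is a descriptive baseline list in a condensed article, and the full protocol may cover it. Data monitoring also collects hospitalization.
- **That a significant fall triggers roll-out.** No such rule is stated, and the wider-application sentence is hedged.

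**Conclusion.** The concern holds as a mismatch between claim and design. The effectiveness aim is not answerable by an uncontrolled before-after comparison in 20 people selected on severity, with other treatment allowed. This conclusion follows from the design alone and needs no numerical assumption.

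The amount of non-specific change is unknown. The 1.1 to 5.5 GUS units rest on assumed r and k, are upper bounds for regression to the mean under those values, and leave out natural recovery and co-treatment, for which the document gives no basis. They show only that a fall near the 5-unit target could contain a material part unrelated to iCBT. The significance probabilities further assume an SD of change of 11.

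The feasibility and acceptability aims are unaffected. The point should be corrected before recruitment, which had not begun at submission, but it is no reason to stop the study.

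**What to change.** 1. **Aim.** In the Abstract (Background and Methods), the last sentence of the Introduction, and both places in the Discussion, replace the effectiveness aim with: to assess feasibility and acceptability, and to estimate within-person change after iCBT, with 95% confidence intervals, to inform a later controlled trial.
2. **Use of results.** Make the practice statement in the Abstract (Discussion) and the wider-application statement in the Discussion conditional on the result of that trial. Name regression to the mean, natural recovery and changes in co-treatment as limits on attribution.
3. **Co-treatment.** If the full protocol does not already do so, record starts, stops and changes of other gambling or psychiatric treatment at T1, T2 and T3. Report them descriptively, with no inferential subgroup analysis. This only documents other care; it does not alter what participants are permitted to continue, and it does not replace a control group.

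Cost: a few sentences, one short form at assessments already planned, and a more modest claim. Sample size, visits and intervention need no change on account of this point.

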**Methods:**

This non-randomized pilot and feasibility study will recruit 20 people with GD. All participants will receive the iCBT intervention through self-learning videos and guided weekly group sessions. The effectiveness of the intervention will be assessed at baseline (week 0), post- treatment completion (week 10), and 6 weeks post-treatment (week 16). The outcomes measured will be the change in gambling symptoms, gambling urges, cognitive distortions, readiness to change, emotional problems, and quality of life of the participants.

**Discussion:**

The feasibility of iCBT for GD patients in Indonesia will be assessed by this study. The study’s results will give an indication of the acceptability of the intervention and the feasibility of a subsequent conclusive trial. The delivery of iCBT may help to address the issue of treatment access in an extensive geographical region and provide immediate implications as a treatment resource for GD in practice.

## Introduction

According to the Diagnostic and Statistical Manual of Mental Disorders (DSM-5), gambling disorder is defined as a persistent and recurrent problematic gambling behavior that results in substantial clinical impairment or distress.
^
1
^ The issue of gambling disorder (GD) is growing worldwide. In recent years, more people have access to both offline and online gambling. In addition, the COVID-19 pandemic corresponded with an increase in online gambling platforms.
^
3
^
^,^
^
4
^ A study in Indonesia during the pandemic found the prevalence of GD in Indonesia is estimated to be 1% in 2021.
^
2
^ This is an enormous figure as Indonesia comprised up to 278 million people.
^
3
^Low public awareness and a lack of effective regulation could eventually cause the number of individuals experiencing GD to rise in the future.
^
3
^
^,^
^
5
^

Gambling disorder causes major impacts in life including unemployment, interpersonal problems, financial difficulties, and an increased risk of other mental disorders such as depression, anxiety disorders, stress-related and somatoform disorders, along with substance use disorder.
^
2
^ Therefore, it is essential to provide suitable treatment for gambling disorders. Early intervention and appropriate management have been shown to significantly improve outcomes for individuals with gambling disorders.
^
6
^
^,^
^
7
^

The goal of GD treatment is symptom remission and functional recovery. To date, no pharmacological treatment has been approved for GD. However, some studies have demonstrated positive outcomes when pharmacological and psychotherapy treatments are combined.
^
8
^ Cognitive behavioral therapy (CBT) is an effective treatment modality for GD.
^
8
^
^,^
^
9
^ Studies reveal that CBT reduces gambling-related symptoms and problematic behavior whilst also improving the overall functioning and quality of life of people with GD.
^
7
^
^,^
^
9
^ In recent years, internet-based cognitive behavioral therapy (iCBT) has been suggested as a means of lowering barriers to professional help seeking by showing equally promising outcomes with increased accessibility, convenience, and cost-effectiveness.
^
10
^
^–^
^
12
^ Studies of help-seeking among individuals with gambling problems consistently report very few gamblers seek formal help, with only 1 in 25 moderate-risk gamblers have sought help for gambling-related issues, and 1 in 5 people with problem gambling have engaged in similar help seeking actions.
^
5
^ Similar findings also come from an Indonesian study that indicated only 15.5% of people seek treatment for GD.
^
2
^ Problem gambling and its consequences can remain hidden within families, usually over extended periods, and help-seeking is often the last resort after significant adverse events or crises such as family breakdown, loss of employment, legal issues, or deterioration of mental health.
^
13
^
^,^
^
14
^ Since delivering treatment for gambling disorders is challenging in Indonesia due to its vast and varied territory, iCBT appears to be a promising treatment option. However, research regarding the effectiveness of iCBT is still very scarce in Indonesia. This pilot study aims to examine the effectiveness, acceptability and feasibility of iCBT for GD in Indonesia.

PROTOCOL

## Methods

### Study design

This study is a pilot and feasibility study with a quasi-experimental design. The protocol adheres to the Standard Protocol Items: Recommendations for Interventional Trials (SPIRIT) checklist (Extended data: Supplementary file 1).
^
15
^ After intake screening, participants will undergo baseline assessment (T1) and will be given treatment for 10 weeks. The treatment will consist of individual online learning sessions delivered through pre-recorded videos, followed by weekly online group therapy sessions with a therapist. Each group therapy session will include five participants. This will be followed by follow up assessment immediately after treatment (T2) and follow up assessment 6 weeks after treatment (T3) (
Figure 1).

**Figure 1. f1:**
[figure not shown]
Study flowchart.

### Participants and settings

A total of 20 participants screened as probable pathological gambler (indicating severe and pervasive problem gambling) based on South Oaks Gambling Screen (SOGS) will be recruited using online advertisements via social media and through consecutive sampling by directly approaching current and former patients in inpatient and outpatient services in Cipto Mangunkusumo Hospital, Indonesia. All participants will be allowed to continue their prior treatment as indicated.

The inclusion criteria include age between 18-59 years old, fluent in Bahasa Indonesia, be diagnosed as person with GD using ICD-11 by medical doctors at [name] General Hospital, Jakarta, Indonesia. Exclusion criteria are no history of gambling in the past six months, history of severe psychiatric disorder (i.e., psychotic disorders, severe mood disorders, and intellectual disability), history of neuropsychiatric disorders (e.g., seizures), and inability to access web browsers and online conferencing platforms. There will be no drop out criteria in this study. Adherence to the treatment will be evaluated to optimize the configuration of the iCBT for future studies.

The South Oaks Gambling Screen is chosen as a screening tool because of its widespread use internationally.
^
16
^ The adaptation to Indonesian version in community setting yielded a good validity and reliability testing, indicating SOGS as a good instrument to screen for GD in Indonesia.
^
2
^

Following the determination of a participant’s eligibility, several instruments will be employed to assess the effectiveness of the study. The primary outcomes will be evaluated using the Indonesian version of the Gambling Symptom Assessment Scale (G-SAS) to measure gambling symptoms, the Gambling Urge Scale (GUS) to assess gambling urges, and the Gambling Related Cognitions Scale (GRCS) to evaluate cognitive distortions. Secondary outcomes will be measured using the Barratt Impulsiveness Scale-11 (BIS-11) to assess impulsivity, the University of Rhode Island Change Assessment Scale (URICA) to gauge readiness to change, the World Health Organization Quality-of-Life Scale (WHOQOL-BREF) to evaluate quality of life, and the Self Rating Questionnaire-20 (SRQ-20) to assess emotional problems.
^
17
^
^–^
^
27
^ The assessment schedule is presented in
Table 1 and
Figure 2.

**Table 1. T1:** Outcome and measurement.

Outcome	Measurement	Data for analysis	Type and score range	Hypothesis	Assessment time point		
					T1	T2	T3
Gambling symptom severity	G-SAS	Sum of 12 items	Continuous, 8 (mild) to 48 (extreme)	Lower	v	v	v
Gambling urges	GUS	Sum of 6 items	Continuous, 0 to 42, the higher the score indicating the higher the urges/craving	Lower	v	v	v
Gambling- related cognitive distortions	GRCS	5 domains, with the highest percentage being the most dominant domain.	Continuous, 0% to 100% per domain	Lower	v	v	v
Impulsivity	BIS_11	Sum of 30 items	Continuous, 30 to 120, the higher the score indicating the higher levels of impulsivity	Lower	v	v	v
Readiness to change	URICA	Means of each stage of change score	Continuous, means of 9.3 (pre-contemplation), 11 (contemplation) and 12.6 (participation)	Lower	v	v	v
Nonspecific psychological distress	SRQ-20	Sum of 20 items	Continuous, 0 to 20, with scores >5 indicating mental distress	Lower	v	v	v
Quality of life	WHOQOL- BREF	4 domains, with transformed score used	Continuous, 0 to 100 per domain, the higher the score the higher the quality of life	Higher	v	v	v

G-SAS, Gambling Symptom Assessment Scale; PGSI, Problem Gambling Severity Index; GUS, Gambling Urge Scale; GRCS, Gambling Related Cognitions Scale.

**Figure 2. f2:**
[figure not shown]
Study timeline.

### Development of the iCBT

The iCBT module was developed by researchers from Department of Psychiatry, Faculty of Medicine, Universitas Indonesia and Department of Psychiatry, Flinders Centre for Gambling Research, South Australia. This module consists of 6 parts which will be used as a guide for the therapist in the therapy sessions. The module content for each session is described in
Table 2.

**Table 2. T2:** Description of iCBT module content.

Session	Content	Behavior Change Technique ^ 28 ^	Delivery	Targetted Outcome
1	Building rapport and assessment	-	Online video and online group CBT session	URICA, SRQ-20, WHOQOL-BREF
2	Psychoeducation and objectives	• Goal-setting (behavior) • Goal-setting (outcome) • Discrepancy between current behavior and goal • Pros and cons • Verbal persuasion about capability • Commitment	Online video and online group CBT session	Improvement in GUS, GSAS, GRCS score
3	Understanding gambling disorder Exposure therapy (first exposure task)	• Information about health consequences • Information about social and environmental consequences • Information about emotional consequences • Exposure	Online video and online group CBT session	Improvement in GUS, GSAS, GRCS, and BIS11 score
4	Identification of gambling thoughts and cravings Review of first exposure therapy task and planning of next exposure task	• Problem-solving • Exposure • Graded tasks • Feedback on behavior	Online video and online group CBT session	Improvement in GUS, GSAS, GRCS, and BIS11 score
5-9	Exposure therapy	• Problem-solving • Exposure • Graded tasks • Feedback on behavior	Online video and online group CBT session	Improvement in GUS, GSAS, GRCS, and BIS11 score
10	Relapse and prevention strategies	• Problem-solving • Review outccome goals • Commitment	Online video and online group CBT session	

The contents of iCBT module are largely derived from The Flinders/Statewide Gambling Therapy Service (SGTS) Model of Treatment for Gambling Disorders, a manualized CBT treatment program.
^
29
^
^,^
^
30
^ The beginning of the program addresses topics such as the severity of gambling, the level of motivation, comorbidities, money management, and support systems. The intervention approach then provides psychoeducation and outlines objectives of the therapy for the participants and their significant others, aiding them with the understanding of gambling behavior, and how to identify distorted gambling thoughts and correct them. Exposure therapy including guided imagery is introduced and used to extinguish urges. Relapse prevention strategies are also included with ways to implement a balanced lifestyle, managing lapses and relapses, and ongoing money management.

